### Sample size

The trial is powered to detect a standardised effect size of 0.267 (equivalent to a 4-point change) on the Dementia Quality of Life (DEMQOL) [42] and assuming a standard deviation of 15 points in DEMQOL [42] scores. In this population, this effect size is equivalent to the smallest change that could be considered clinically meaningful. Assuming a correlation of 0.6 between baseline and 36-week follow-up DEMQOL scores [42] and an attrition rate of 20% at follow-up (a conservative estimate based on the 12%–15% rates observed by Wenborn *et al*., 2008 [43]), the trial will need to recruit 354 participant dyads at baseline (177 per arm) in order to achieve 80% power to detect the aforementioned effect size at the two-sided 5% level of significance.

### Outcome measures

#### Primary outcome

The primary outcome will be QoL of the PwD, as rated by the PwD directly, using DEMQOL [42], at week 36 (W36). DEMQOL is a 29-item interviewer-administered, self-report questionnaire with good psychometric properties in persons with mild to moderate dementia (good internal consistency and test–retest reliability and moderate validity) (see Table 3) (Additional file 1).

**Table 3 Tab3:**
[figure not shown]
Schedule of the SENSE-Cog randomised controlled trial, according to SPIRIT checklist. * Also during sensory support therapist visits for those allocated to the sensory intervention group. Abbreviations: PwD participant with dementia, W week

#### Secondary outcomes

For the person with dementia:QoL assessed by DEMQOL at W18QoL assessed by DEMQOL Proxy, at W18 and W36, rated by the companionscores of the following measures at W18 and W36:○ functional ability, assessed by the following scales:▪ Bristol Activities of Daily Living scale [44];▪ Veterans Affairs Low Vision-Visual Functioning Questionnaire [45];▪ Veterans Affairs Low Vision-Visual Functioning Questionnaire Spousal rating [45];▪ Hearing Handicap Inventory for the Elderly [46];▪ Hearing Handicap Inventory for the Elderly Spousal rating [47].○ global cognitive functioning, using the MoCA scale [30].○ behavioural and psychological symptoms of dementia, assessed by the 12-item Neuropsychiatric Inventory [48].○ relationship with companion, assessed by the Relationship Satisfaction Scale [49].

For the companion:mental well-being and QoL using the 12-item General Health Questionnaire [50] and health utility using the Short Form-12 Health Survey [51] (Brazier and Roberts, 2004 [51]), at W36;scores of the following measures at W18 and W36○ companion experience, assessed by the Family Caregiving Role scale [52];○ relationship with PwD, assessed by the Relationship Satisfaction Scale [49];○ companion anxiety and depression, assessed by the Hospital Anxiety and Depression scale [53].

Health economic outcomes:health-care resource utilisation from baseline to W18 and W36 collected using the RUD-Lite instrument [40] with the companion;health utility, ascertained at baseline, W18 and W36 from:○ 5-level EuroQol 5-dimension rated by both the PwD and the companion [54];○ Short Form-12 Health Survey [51], rated by both the PwD and the companion.

### Demographics

Demographic information about the PwD and companion will be captured at screening and baseline relating to age, gender, maritial status, living status, current or former occupation, duration and type of memory problem, diagnosis date, years in formal education, date of most recent hearing and vision screen, current medication for dementia and current psycho-social interventions. This will allow screening of eligible participants and will allow analysis of the potential influence of demographic differences on outcome variables within and between sites.

### Study procedures

#### Timeline

Start of inclusion period: first quarter of 2018;duration of the inclusion period: 21.5 months;duration of participation of each participant: 36 to 40 weeks (that is, around 9 to 10 months);total duration of the study: 33–34 months.

#### Initial screening visit

Cognition will be assessed by MoCA [30]. Hearing will be screened by using “HearCheck” [33] (a simple hand-held screening device). Vision will be screened by using the “PEEK Acuity App” [31] alongside the confrontation visual field test: “Can you see my hands?” [32].

#### Baseline visit

The baseline visit is conducted at the PwD’s home or clinic by a researcher. PwD and companion complete a battery of scales (around 2 h) (Table 4). The baseline visit may be conducted the same day as the screening visit (but after the screening procedures) if the PwD and the companion meet the eligibility criteria. This baseline visit may also be split into two visits (depending on the PwD or the companion’s preference). The second baseline visit must be conducted within 2 weeks of the first baseline visit.

**Table 4 Tab4:** Battery of scales administered during baseline, week 18 and week 36 visits

Outcome	Administered by	Information about	Scale
QoL of PwD	Researcher to PwD	PwD	DEMQOL [42]
	Researcher to companion	PwD	DEMQOL proxy [42]
Dementia-related functional ability	Companion self-completes	PwD	BADLs [44]
Vision-related functional ability	Researcher to PwD	PwD	LV-VFQ – 20 [45]
	Researcher to companion	PwD	LV-VFQ – SP
Hearing-related functional ability	Researcher to PwD	PwD	HHIE-25 [46]
	Researcher to companion	PwD	HHIE-SP [47]
Global cognitive functioning	Researcher to PwD	PwD	MoCA (at screening) [30]
Behavioural and psychological symptoms	Researcher to companion	PwD	NPI-12 [48]
Relationship with companion	Researcher to PwD (not in presence of companion)	PwD	RSS [49]
Mental well-being of companion	Companion self-completes	Companion	GHQ-12 [50]
QoL of companion	Researcher to companion	Companion	SF-12 [51]
Companion experience	Companion self-completes	Companion	FCS [52]
Relationship with PwD	Companion self-completes	Companion	RSS [49]
Companion depression	Companion self-completes	Companion	HADS [53]
Health resource utilisation	Researcher to companion	PwD	RUD-Lite [40]
	Researcher to companion	PwD	EQ-5D-5 L Proxy [54], SF-12 Proxy [51]
	Researcher to PwD	PwD	EQ-5D-5 L [54], SF-12 [51]

*Abbreviations*: *BADLs* Bristol Activities of Daily Living, *DEMQOL* Dementia Quality of Life, *EQ-5D-5 L* 5-level EuroQol 5-dimension, *EQ-5D-5 L-P* 5-level EuroQol 5-dimension Proxy, *FCS* fluorescence correlation spectroscopy, *GHQ-12* General Health Questionnaire – 12 items, *HADS* Hospital Anxiety and Depression Scale, *HHIE-25* Hearing Handicap Inventory for the Elderly - 25 items, *HHIE-SP* Hearing Handicap Inventory for the Elderly Spousal rating – 25 items, *LV-VFQ – 20* Veterans Affairs Low*-*Vision Visual Functioning Questionnaire – 25 items, *LV-VFQ – SP* Veterans Affairs Low*-*Vision Visual Functioning Questionnaire Spousal rating – 25 items, *MoCA* Montreal Cognitive Assessment, *NPI-12* Neuropsychiatric Inventory – 12 items, *PwD* people with dementia, *QoL* quality of life, *RSS* Relationship Satisfaction Scale, *RUD-Lite* Resource Utilization in Dementia-Lite, *SF-12* Short Form-12 Health Survey

### Data protection and sharing

We will follow best practice in accordance with current UK General Data Protection Regulation (GDPR) guidance and adhere to the Guidelines for Data Management in Horizon 2020 and local guidelines for each site; no patient identifiable data (PID) will be transferred across sites. All PID will be kept separately from the anonymized data to be entered in the case report form (CRF). The University of Manchester institutional repository (Research Data Management Service) will cater for the publishing and sharing of research data. Data will be made available through the University of Manchester institutional repository (Research Data Management Service). Research data will be made available together with appropriate metadata in line with Horizon 2020 policy to enable other researchers to identify whether the data could be suitable for re-use. Published outputs will be assigned a Digital Object Identifier to reference the data in publications. Anonymised data will eventually be made open access and this will also be made clear to participants before they consent.

### Randomisation and allocation concealment

Randomisation will be performed no later than 3 days following baseline. Randomisation will be conducted through the trial electronic case report form (eCRF) [55]. One person in each site will perform randomisation. One person from the research team will be identified in each site to perform randomisation, excluding the blinded researcher who will undertake the outcome visits. Randomisation will be stratified by centre. Once participants are allocated to the eCRF, eligibility criteria (including signed informed consent) must be met to allow for randomisation online. The SST will then trigger the local procedure for sensory assessment and provision of hearing aids/glasses for those participants allocated to the SI group.

The randomisation code will be maintained by the European Clinical Trials Platform & Development (EUCLID) Coordinating Trial Unit (CTU). The blinded researcher and the statistician team will not have access to the randomisation code. To ensure allocation concealment, full details of the randomisation scheme will not be disclosed.

### Blinding

It will not be possible for participant dyads to be blinded to the allocation they receive on randomisation. Thus, each centre will have both blinded and un-blinded researchers involved with different aspects of the study. The SST will not be blinded. The outcome rater (blinded researcher) will be blinded and every attempt to maintain this blind will be made. To achieve this, when the follow-up visits are booked by the SST, the participant dyad will be reminded to make every effort not to reveal whether they had received the intervention or not. This will include keeping study-related materials (including new devices such as hearing aids, special lamps or other sensory support devices or materials) out of sight during the outcome rating visit.

During follow-up visits, an un-blinded researcher will administer MoCA [30] and HHIE (Hearing Handicap Inventory for the Elderly - 25 items) [46] with the PwD still wearing hearing aids and glasses if required. The blinded researcher will conduct the remainder of the measurement scales while the participant is wearing glasses but not hearing aids. Since most of the outcome measures will be undertaken with the companion as informant for either themselves or the PwD, this should not interfere with the integrity of the outcome measures.

For the blinded researcher, ratings will be ascertained of their perception of allocation of participant dyads to determine the strength of the allocation concealment. At W18 and W36, blinded researchers will rate a Likert-style scale [56] (completely certain, somewhat certain, some doubt, not at all certain, or complete guess) of their perception of which group the participant dyad has been assigned to. This will be analysed to ascertain the proportion of blinded researchers who are correct, incorrect or neutral for treatment allocation at W18 and W36.

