Glasses or hearing aids (or both) will be prescribed, administered and fitted to participants, according to their needs, by vision specialists (optometrist, ophthalmologist or optician) and audiologists, respectively, in the participant’s home or in the clinic within 6 weeks after full assessment (stage 1). Essilor International [35] will provide the glasses lenses and yellow filters for the study. Starkey Hearing Technologies [36] will provide the hearing aids and two pocket talkers (http://www.starkey.co.uk/hearing-aids/hearing-amplifiers) per site. The hearing devices used for this trial will be behind-the-ear (BTE)-style hearing instruments (specifically, Starkey Muse i2400 Mini BTEs in silver). Supplementary sensory devices (lamps and glasses straps) may be supplied according to participant needs by the SST throughout the SI (Table 2).

**Table 2 Tab2:** SENSE-Cog Randomised Controlled Trial Sensory Intervention sensory devices to be supplied, who pays costs and duration

Device	Supplier	Cost	Duration
Hearing aid: Muse i2400 Mini Behind the ear	Starkey Hearing Technologies	Free to participant	Participant keeps during and after study
Personal listening amplifier	Accredited supplier such as Mini Tech, Pocket Talker, or equivalent	Free to participant	Return after study and option to purchase at participant’s own expense
Additional auditory or visual equipment as advised by the sensory support therapist	Starkey Hearing Technologies or other specialist suppliers	Participant’s own expense	Participant keeps during and after study
Glasses lenses (including yellow filters if needed)	Essillor International	Free to participant	Participant keeps during and after study
Glasses frames (participant choice)	Local optician	Free basic frames or other frames at participant’s own expense	Participant keeps during and after study
Lamp	Any supplier provided that the required criteria are met	Free to participant	Return after study and option to purchase at participant’s own expense
Glasses straps	Croakies or equivalent supplier	Free to participant	Participant keeps during and after study

Stage 3: Sensory support

The SST will support participants with the following '*primary*' (all participants receive) and '*secondary*' (received if needed by individual) components across a maximum of 10 visits over 18 weeks after randomisation (see Fig. 1):

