### Care as usual

The CAU group provides a comparison with the SI group. CAU participants will receive no additional intervention other than hearing and vision screening assessment. CAU participants will be informed of any suspected hearing or visual impairment (or both) identified on screening and information sheets provided about where they may access further support through their general practitioner or standard routes of referral. Thus, we except a small increase in subsequent diagnosis of sensory impairment compared with usual care but no effect on prescription of appropriate correction and adherence. Thus, effect estimate of the SI compared with this CAU group should be slightly decreased and conservative regarding type I error rate. Differences in access of health services between the intervention group and CAU group will be captured by the health economic evaluation measure (Resource Utilization in Dementia-Lite, or RUD-Lite) [40].

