### Follow-up visits

At 18 weeks (± 2 weeks) and 36 weeks (± 2 weeks), researchers will visit the PwD and their companion to complete the same battery of scales as at the baseline visit (Table 4). If a second visit is required because of fatigue, this will take place within 2 weeks following the first.

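### At weeks 18 and 36 the blinded rater is left to give RUD-Lite and sees possibly trial-supplied glasses: avoidable unblinding cues around the primary DEMQOL interview

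*Protocol article*

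**What the plan says.** All references are to the protocol article.

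- **Who gives which scale.** Under Blinding, MoCA and HHIE go to an un-blinded researcher at follow-up, with hearing aids and glasses worn if required. Then: "The blinded researcher will conduct the remainder of the measurement scales while the participant is wearing glasses but not hearing aids".
- **What the remainder contains.** Table 4 (Baseline visit) lists RUD-Lite as given by a researcher to the companion. Follow-up visits repeats the Table 4 battery at weeks 18 and 36. Secondary outcomes confirms it: "health-care resource utilisation from baseline to W18 and W36 collected using the RUD-Lite instrument [40] with the companion".
- **What RUD-Lite is expected to show.** Care as usual states: "Differences in access of health services between the intervention group and CAU group will be captured by the health economic evaluation measure".
- **What is hidden.** Dyads are asked not to reveal their allocation. Under Blinding this includes "keeping study-related materials (including new devices such as hearing aids, special lamps or other sensory support devices or materials) out of sight". Hearing aids and lamps are named there; glasses are not.
- **What the intervention arm may receive.** Stage 2 and Table 2 (Sensory intervention) provide lenses, yellow filters where needed, and straps, according to the participant's needs.
- **The primary outcome.** DEMQOL at week 36, answered by the person with dementia in an interview (Primary outcome).

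**The concern.** The trial describes itself as observer-blind, and dyads know their allocation. The rater's blind is meant to keep the interviewer's expectations out of the interviewer-administered scales, the primary DEMQOL among them.

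Two instructions work against it. First, the blinded rater has to ask an unblinded companion about service use, with an instrument that the plan itself expects to differ by arm. The same companion has been asked to conceal allocation. The intervention generates contacts of its own: sensory assessment, fitting, up to 10 therapist visits, and referral to other services where needed. Second, new devices are to be out of sight, yet glasses stay on in front of the rater.

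The Blinding section reassures the reader that most outcomes come from the companion. That does not cover this point: the primary DEMQOL is given to the person with dementia, and the companion is the RUD-Lite informant.

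**Working it through.** **Step 1. Trace the task allocation.**

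| Element | Where stated | Result |
|---|---|---|
| Un-blinded researcher at follow-up | Blinding | MoCA and HHIE only |
| Blinded researcher at follow-up | Blinding | all remaining scales |
| RUD-Lite mode | Table 4 | researcher to companion |
| RUD-Lite timing | Secondary outcomes; Follow-up visits | weeks 18 and 36 |

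RUD-Lite therefore falls to the blinded researcher at both follow-up visits.

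**Step 2. Is it a cue?** Care as usual expects group differences in service access to appear on RUD-Lite. That makes it a plausible cue. It does not make it a certain one for any single dyad, because the instrument's items are not in the document.

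**Step 3. Glasses.** The two instructions under Blinding pull apart: hide new devices, but wear glasses before the rater. Care as usual expects no effect of screening on prescription of correction in that arm, so on the plan's own expectation newly acquired glasses would lean towards the intervention arm. They do not identify it (see the objection).

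**Step 4. Route to the primary outcome.** Randomisation and allocation concealment speaks of the blinded researcher, in the singular, undertaking the outcome visits. This suggests, but does not fix, the same person at weeks 18 and 36. If the rater does return, giving DEMQOL first at week 36 does not remove what was learned at week 18. The order of scales within a visit is not stated, nor is the moment at which the allocation guess is recorded.

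**Step 5. Reproduce the plan's sample size, to obtain a standard error.** Inputs from Sample size: effect 0.267 SD, SD 15, correlation 0.6, attrition 20%, power 80%, two-sided 5%.

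- Adjusted SD = 15 × √(1 − 0.6²) = 12.
- Difference = 0.267 × 15 = 4.005.
- n per arm = 2 × [12 × (1.960 + 0.842) / 4.005]² ≈ 140.9, so 141.
- With attrition: 141 / 0.8 = 176.25, so 177 per arm and 354 in total. This matches the plan. (A difference of exactly 4 gives 356.)
- Retained per arm: 177 × 0.8 = 141.6; power for a 4-point difference is 80.1%.
- SE of the adjusted difference = 12 × √(2 / 141.6) ≈ 1.43 points.

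**Step 6. Illustration only.** Let *b* be an assumed average bias between the arms due to rater knowledge. With no true effect, the rejection rate is 1 − Φ(1.96 − *b*/SE) + Φ(−1.96 − *b*/SE).

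| Assumed *b* (DEMQOL points) | *b*/SE | Two-sided type I error |
|---|---|---|
| 0 | 0 | 5.0% |
| 0.5 | 0.35 | 6.4% |
| 1.0 | 0.70 | 10.8% |
| 1.5 | 1.05 | 18.3% |
| 2.0 | 1.40 | 28.9% |

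Here *b* is an average over all dyads. A 1-point shift arising in only half of them averages 0.5 × 1 = 0.5 point, so the 6.4% row would apply. Nothing in the document says which row, if any, is realistic.

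**The case against.** A reader might infer that the procedure breaks the blind before the primary rating in every dyad followed at week 18. The documents do not support that, for these reasons.

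- **RUD-Lite.** A difference between arm means need not reveal one dyad's arm. Nothing shown says that the instrument asks about therapist visits or study devices. Care-as-usual dyads are told of a suspected impairment and directed to routine services, so they too may report sensory care.
- **Glasses.** They are supplied according to need, people with hearing loss only are eligible, and care-as-usual participants may already own glasses or obtain them. Straps arguably fall under the existing request to hide study materials.
- **Carry-over.** Neither the same rater at both visits nor the order of scales is fixed, and DEMQOL is the first row of Table 4.
- **Other safeguards.** The rater's blind is not the trial's only protection. The statistics team has no access to the randomisation code, the blinded researcher does not perform randomisation, and details of the scheme are withheld. The rater's guess at allocation is recorded at weeks 18 and 36.
- **Indirect route.** DEMQOL is answered by an unblinded person with dementia. Rater expectation is only one path to bias, and another stays open whatever is done with RUD-Lite.

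All of this stands, and it limits the point to avoidable exposure. It does not remove the point: the task allocation is explicit, the two device instructions still conflict, and recording a guess measures unblinding without preventing it.

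**Conclusion.** The point holds as an avoidable weakness in the blinding procedure. The blinded rater is assigned a companion interview that the plan expects to differ by arm, twice, and sees glasses that may be new while other new devices are hidden. Knowledge gained at week 18 could reach the week-36 DEMQOL if the same rater returns.

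The size is unknown. The type I error figures of about 6.4% and 10.8% rest on assumed average biases of 0.5 and 1 point, together with the plan's SD, correlation and attrition. They show sensitivity, not an expected effect. The sample size itself reproduces and is not in question. The change is worth making because it costs little and protects the interviewer-administered primary outcome.

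**What to change.** 1. Under Blinding, add RUD-Lite at weeks 18 and 36 to the scales given by the un-blinded researcher, who already attends for MoCA and HHIE. Both visits matter because of possible carry-over. Baseline can stay as it is, since it precedes randomisation.
2. State that the blinded rater gives DEMQOL first at each follow-up and records the allocation guess immediately after it, before the other scales.
3. Reconcile the wording on glasses with the rule that new devices be kept out of sight, saying explicitly how trial-supplied glasses, filters and straps stand under that rule.

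**Cost.** A shift of tasks between two researchers already involved in the follow-up visits and a change to the visit guide, with no added staff or visits. RUD-Lite, which feeds the economic analysis, would be collected unblinded, and the un-blinded part of the visit becomes slightly longer.

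Having the future un-blinded researcher do the baseline visit, so that the rater never sees the earlier glasses, is not recommended. It would put different DEMQOL interviewers at baseline and follow-up, which may add interviewer variation and weaken the 0.6 correlation on which the sample size depends.

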### Follow-up visits

At 18 weeks (± 2 weeks) and 36 weeks (± 2 weeks), researchers will visit the PwD and their companion to complete the same battery of scales as at the baseline visit (Table 4). If a second visit is required because of fatigue, this will take place within 2 weeks following the first.

